# Multimodal cerebral imaging study on the effects of “Adjust Zang Dredge Meridian” electroacupuncture on cerebral central sensitization in PDPN patients: a study protocol for a sham-controlled, randomized trial

**DOI:** 10.1186/s13063-021-05773-w

**Published:** 2021-11-13

**Keywords:** Electropuncture, Painful diabetic peripheral neuropathy, Central sensitization of the brain, Functional magnetic resonance imaging; Clinical trial

## Abstract

**Background:**

Painful diabetic peripheral neuropathy (PDPN) has a great impact on an individual’s quality of life. The current researchers’ previous trial suggested that acupuncture was a promising adjunctive treatment for PDPN. However, the underlying mechanism of action of acupuncture treatment for PDPN is still unclear, especially its effects at the cerebral level. The aim of this trial will be to explore how acupuncture works in treating PDPN by using multimodal cerebral imaging.

**Method and design:**

This will be a randomized controlled trial. A total of 150 participants will be recruited and assigned to one of three groups: the healthy group, the DM without PDPN group and the DM with PDPN group. Participants in the DM without PDPN and the DM with PDPN groups will each be further divided between an electroacupuncture group and a sham electroacupuncture group. Participants will receive six treatment sessions per week for 4 weeks. Multimodal cerebral imaging includes resting-state functional magnetic resonance imaging (rs-fMRI), diffusion tensor imaging (DTI) and magnetic resonance spectroscopy (MRS); this neurophysiological testing will be the primary outcome measure. Subjective pain scales and blood analysis will be a secondary outcome measure and will be used to assess the clinical efficacy of the intervention. Multimodal cerebral imaging will be used to detect cerebral activity changes in each treatment group. The clinical data and fMRI data will be analysed for all the groups. Multiple correlation regression analyses will be used to assess the association between changes in cerebral functional activity and the improvement of clinical outcomes after acupuncture treatment.

**Discussion:**

This study is based on the results of the researchers’ previous study, and using combined clinical and cerebral function changes, it will help evaluate the effects of acupuncture on PDPN. The investigation of acupuncture’s central mechanism of action will further expand the understanding of acupuncture treatment of PDPN.

**Trial registration:**

Chinese Clinical Trial Registry ChiCTR1900024109. Registered on 26 June 2019.

**Supplementary Information:**

The online version contains supplementary material available at 10.1186/s13063-021-05773-w.

## Background

Diabetes mellitus (DM) and its complications are serious diseases that harm human health. In 2016, there were approximately 415 million DM patients in the world, or about 8.8% of the global population [1]. In 2019, the 9th IDF Diabetes Atlas, released by the International Diabetes Federation (IDF), shows that there were 116.4 million patients with DM in China, which now ranks as first in the world in the number of DM patients, and this number is expected to reach 142.7 million by 2045 [2]. Diabetic peripheral neuropathy (DPN) is one of the most common complications of DM. In China, approximately 46.6% of DM patients have DPN [3]. Among DPN patients, painful diabetic peripheral neuropathy (PDPN) is a disease that currently lacks effective treatment [3] and has a serious negative impact on a patient’s quality of life [4, 5]. Approximately 11.4% and 40.5% of patients experience severe and moderate pain, respectively, and of these, 3.7% have lower limb ulcers or even required amputations [6]. More than 2/3 of PDPN patients experience varying degrees of problems with depression and anxiety [7, 8], which pose a burden on their families and on society.

PDPN is characterized by distal symmetric polyneuropathy, and the main clinical manifestations are numbness, tingling and abnormal sensations at the end of limbs, which usually start in the lower limbs and are aggravated at night. The pathogenesis of PDPN is very complicated and includes metabolic disorders, vascular injury, nerve injury, oxidative stress and inflammatory responses. In recent years, researchers have generally assumed that peripheral sensitization and central sensitization play an important role in the production and maintenance of PDPN [9–11]. Studies have confirmed [12] that simple peripheral sensitization is not a key factor leading to the occurrence of PDPN. Hyperalgesia and hypersensitivity can still occur after electrical stimulation of the damaged area following anaesthesia. Therefore, central sensitization should be considered a common and core pathological change in PDPN.

In recent years, the rapid development of multimodal cerebral imaging has become an important method in diagnosing nervous system diseases in vivo. Functional magnetic resonance imaging (fMRI) has been widely used in the study of PDPN, and it provides an exact imaging basis for the study of cerebral structure and changes in functional connections [13, 14]. At present, modern medicine is developing new treatment interventions for PDPN, such as blood glucose control, nerve nutrition and pain-management regimens. Although these methods can relieve patients’ pain and other symptoms to varying degrees, it is still difficult to achieve satisfactory treatment effects and to improve patients’ physical symptoms, quality of life and safety [4]. Acupuncture, as an in vitro treatment method with neurological effects, shows unique advantages in the treatment of PDPN. A number of clinical studies have confirmed that acupuncture can significantly improve pain symptoms in patients with PDPN [15, 16]. In recent years, fMRI has also been applied to study the central regulatory mechanism of acupuncture’s effects [17].

“Adjust Zang Dredge Meridian” electroacupuncture is a therapy established by our research group under the guidance of Chinese acupuncture and the theory of meridian Zang Fu; it incorporates our understanding of the aetiology and pathogenesis of diabetes and its complications. In the pathogenesis of PDPN, seven acupoints have been identified, including Feishu (BL13), Pishu (BL20), Shenshu (BL23), Hegu (LI4), Zusanli (ST36), Sanyinjiao (SP6) and Taichong (LR3). In contrast to the classic acupuncture method of manual twirling, electroacupuncture is safer and more effective in providing pain relief. The combination of classic and electroacupuncture can achieve the effects of regulating zang-fu organs, nourishing meridians and regulating qi and tong jing zhi tong. Based on earlier studies, our research group has demonstrated in both clinical and animal experiments that “Adjust Zang Dredge Meridian” electroacupuncture can effectively improve pain thresholds and nerve conduction velocities in DPN [18, 19]. Therefore, in applying our previous research to the pathological changes of PDPN, we intend to use fMRI technology to explore the potential effects of acupuncture’s central mechanism in the treatment of PDPN. In this proposed study, the first objective will be to use fMRI technology to reveal the mechanisms of central sensitization in the brain of PDPN patients. The second objective will be to investigate the correlation between peripheral neuropathy, subjective pain and changes in brain function in patients with PDPN. The third objective will be to analyse the neuromodulatory effect of “Adjust Zang Dredge Meridian” electroacupuncture on the central sensitization of the brain in PDPN patients through a controlled study of electroacupuncture and sham electroacupuncture and thus to reveal “Adjust Zang Dredge Meridian” electroacupuncture’s mechanism of action in improving the central sensitization of the brain in PDPN patients.

## Method

### Study setting/design

This two-armed randomized, sham-controlled clinical trial will be performed at Guang’anmen Hospital (China Academy of Chinese Medical Sciences) and the Affiliated Hospital of Changchun University of Traditional Chinese Medicine. The study protocol has been approved by ethics committees at both participating hospitals. The clinical trial has been approved by the Ethics Committee of the Affiliated Hospital of Changchun University of Traditional Chinese Medicine (CCZYFYLL2018-002) and by Guang’anmen Hospital (China Academy of Chinese Medical Sciences) (2019-070-KY-02), and it was registered with ChiCTR of the Chinese Clinical Trial Registry (NO: ChiCTR1900024109). A flow chart of the trial is shown in Figs. 1 and 2. This study will be reported based on the STandards for Reporting Interventions in Clinical Trials of Acupuncture (STRICTA) checklist [20] and the Standard Protocol Items: Recommendations for Interventional Trials (SPIRIT) checklist [21] (Table 1 and Additional file 1).

**Fig. 1 Fig1:**
[figure not shown]
Flow chart of the study trial. PDPN

5. Practitioner background	5) Description of participating acupuncturists (qualification or professional affiliation, years in acupuncture practice, other relevant experience)	A doctor who has a licence with at least 2 years of clinical practice. They can skillfully use acupuncture. All participants received standardized training to ensure consistent treatment
6. Control or comparator interventions	6a) Rationale for the control or comparator in the context of the research question, with sources that justify this choice	Based on consensus of the PDPN, meridian and acupoint theory, clinical articles and experience, experimental articles, traditional acupuncture
	6b) Precise description of the control or comparator. If sham acupuncture or any other type of acupuncture-like control is used, provide details as for items 1–3 above.	For sham electroacupuncture group, besides BL13, BL23 and SP6, LR3 will be stimulated 30 min per day for 6 days using blunt needles that cannot penetrate the skin. Electrical stimulation will perform with the power cord cut off

### Recruitment method

One hundred fifty participants with or without PDPN will be recruited through, but not limited to the review and screening outpatients at Guang’anmen Hospital, social media networking (WeChat), community advertisements (including the distribution of leaflets via regular community health counselling), media campaigns and other networking.

## Recruitment criteria

### Inclusion criteria for participants with DM with PDPN

Meet the study’s clinical diagnostic criteria of PDPN;Aged 55–65 years (either sex), with a history of diabetes ≥ 5 years;Present with stable vital signs, with blood pressure, heart rate, blood lipids and other indicators within normal limits;Possess normal cognitive and expressive abilities and have no serious cardiovascular and cerebrovascular disease;Manifest no pre-existing peripheral nervous system lesions;Demonstrate a willingness to provide informed consent, participate voluntarily and cooperate with doctors to complete the clinical trial.

### Inclusion criteria for participants with DM without PDPN

Present with a clear history of diabetes ≥ 5 years and a fasting blood glucose (fasting for at least 8 h) ≥ 7.0 mmol/L;Present no symptoms of PDPN;Aged 55–65 years (either sex);Provide a negative CPT test.

### Exclusion criteria

Sensitivity to acupuncture and history of experiencing dizziness when exposed to needles;Aged under 55 years or above 65 years;Women who are pregnant or lactating, women preparing for pregnancy, and individuals with a long history of contraceptive use;Signs or symptoms of serious diabetic complications (such as proliferative retinopathy, diabetic nephropathy and the disappearance of dorsal foot artery fluctuation), combined with hyperthyroidism and other diseases that affect blood glucose;The presence of an autoimmune disease;Patients who have participated in other or similar clinical trials within the past 3 months;Individuals with combined cardiovascular and cerebrovascular disease; liver, kidney, haematopoietic and other serious primary diseases; or neuropathy caused by other factors (such as heredity, trauma, alcoholism, drug poisoning, and hypothyroidism);Individuals with a history of recent corticosteroid use for the treatment of other autoimmune diseases;Individuals with a risk for bleeding or who experienced a bleeding event in the last month.

### Healthy participants

Aged 55–65 years (either sex), medium size;No restrictive religious beliefs, and no bad habits such as tobacco, alcohol, coffee and tea;Absence of work pressure or life pressure during the observation period;Good health, without any cardiovascular or cerebrovascular diseases or other organic diseases;A negative CPT test.

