## Random allocation

Eligible participants will be randomly assigned to three groups: healthy participants (*n* = 30), DM without PDPN participants (*n* = 60) and DM + PDPN participants (*n* = 60). The DM without PDPN and DM + PDPN groups will be randomly divided further into an electroacupuncture group (n = 30) and a sham electroacupuncture group (*n* = 30). We will use a computer program (Random Allocation Software, version 1.0; Msaghaei) [22] to generate this random distribution. The total observation period will be 4 weeks. All three groups will receive 24 sessions of either electroacupuncture or sham electroacupuncture treatment over the 4 weeks (six sessions per week during the treatment period). Before the clinical trial begins, the researchers will provide each participant or his/her legal guardian the details of the clinical study. All participants will be required to provide written informed consent before treatment begins and randomization occurs.

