### Sample size calculation

This proposed study is an RCT whose primary aim is to evaluate the cerebral imaging mechanism of acupuncture to improve cerebral central sensitization and the clinical effect of acupuncture in patients with PDPN. Acupuncture is a complex intervention that differs from other treatments. Its therapeutic effect is changed if the acupoints are altered. No two-arm, randomized, sham-controlled trial has been conducted on this topic. For this reason, we are using our previous clinical experience to calculate the efficacy of electroacupuncture as an intervention [30, 31]. The proposed sample size of this trial was calculated mainly based on the Short-Form McGill Pain Questionnaire and the assumption that after treatment, the average change reported using this questionnaire would be greater for the experimental group than for the control group. The mean difference was 0.81, with a standard deviation of 0.07. Sample size was calculated using a noninferiority comparison. We set the alpha risk (*α*, type 1 error risk) at 0.025, the beta risk (*β*, type 2 error risk) at 0.2 and the critical value (*Δ*) at − 0.1. Calculating by using SAS [32], the sample size result was 24. Thus, according to this sample size calculation, each group should recruit 24 participants. Allowing for a 20% attrition rate in this study, we plan to recruit 150 participants, with 30 in each of the study groups. Healthy participants will not receive any treatment. Each participant will receive 2 rs-fMRI scans to observe different cerebral activities before and after acupuncture treatment.

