## Discussion

Among diabetic patients, approximately 25% develop PDPN. The probability of PDPN is higher in patients with type 2 diabetes (T2DM) [36]. In PDPN, which is most often associated with sensory motor neuropathy, patients may feel burning, pricking or electric pain. Some patients may even describe hyperalgesia or abnormal pain [37, 38], which greatly reduces their quality of life. Acupuncture is a nonpharmacological treatment. It is very effective for pain relief, especially for PDPN. A Japanese study showed that 20 patients with PDPN who received acupuncture treatment had better pain relief than the patients in the drug treatment group [39]. Another study confirmed that acupuncture can effectively improve the main symptoms of patients with PDPN, significantly reducing or even ending drug use [40]. There is still a lack of clear reporting on the mechanism of acupuncture in the treatment of PDPN. Acupuncture can act on all parts of the central nervous system, and it can exert analgesic effects by regulating neurotransmitters and signalling pathways and immune responses [41]. Using multimodal cerebral imaging technology, Zhou [42] found that electroacupuncture at Weizhong (BL40) and Dachangshu (BL25) can change the cerebral function pain centre and cerebral default network. Therefore, this clinical trial aims to determine whether acupuncture can improve the state of cerebral central sensitization in patients with PDPN. We will use rs-fMRI to better explore the neuroregulatory effect of acupuncture on PDPN cerebral central sensitization and to improve the overall efficacy of acupuncture.

To date, high-quality clinical evidence for acupuncture in PDPN is still insufficient because most clinical trials have had small sample sizes, short or nonexistent follow-up or other unavoidable restrictions. The design of this study takes into account the placebo effects, so two sham acupuncture groups will be set up for comparison. To avoid deviations in the results and improve the reliability of the clinical data, we will try to maintain the consistency of the baseline. Participants will be strictly selected according to the inclusion and exclusion criteria. The rs-fMRI of all participants will be carried out in the MRI room of Guang’anmen Hospital (China Academy of Chinese Medical Science). Our research will help explore the potential clinical applications of acupuncture.

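### Only the healthy volunteers are screened for tobacco, alcohol, coffee, tea and stress, so healthy-versus-diabetic imaging differences cannot be separated from differences in habits and stress

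*Protocol article*

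**What the plan says.** Under Healthy participants, the protocol article requires "no bad habits such as tobacco, alcohol, coffee and tea;Absence of work pressure or life pressure during the observation period".

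The diabetic lists have no counterpart. For DM without PDPN, after diabetes history and fasting glucose, the criteria are "Present no symptoms of PDPN;Aged 55–65 years (either sex);Provide a negative CPT test". For DM with PDPN, the nearest item is "Present with stable vital signs, with blood pressure, heart rate, blood lipids and other indicators within normal limits", which concerns vital signs and laboratory values. The Exclusion criteria mention alcohol only in excluding "neuropathy caused by other factors (such as heredity, trauma, alcoholism, drug poisoning, and hypothyroidism", which does not limit ordinary drinking, smoking, coffee, tea or stress.

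Random allocation sets 30 healthy participants beside "DM without PDPN participants (*n* = 60) and DM + PDPN participants (*n* = 60". Sample size calculation states: "Healthy participants will not receive any treatment". Random allocation also says that all three groups receive treatment sessions, which conflicts with this. Because it divides only the two diabetic groups into electroacupuncture and sham, I take the healthy group to be untreated. The abstract adds: "The clinical data and fMRI data will be analysed for all the groups".

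On comparability, the Discussion says only that "we will try to maintain the consistency of the baseline", through strict application of the entry criteria.

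**The concern.** An untreated group that is scanned and analysed with the others has one evident use: as the reference for what a brain without diabetes looks like. The first objective in the Background, to reveal mechanisms of central sensitization in PDPN, invites that comparison.

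Nicotine, alcohol, caffeine and stress can plausibly shift resting BOLD signal, connectivity and metabolite levels. The criteria remove them from the reference group and leave them unrestricted in the diabetic groups. Strict application of the criteria, which the Discussion relies on for comparability, produces the imbalance for these factors.

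At stake is the reading of any difference from the healthy group. It could be reported as an effect of diabetes or a sign of central sensitization when part of it comes from how the reference group was chosen.

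**Working it through.** **Step 1: compare the criteria.**

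| Factor | Healthy | DM without PDPN | DM with PDPN | Exclusion criteria |
|---|---|---|---|---|
| Tobacco | not allowed | no rule | no rule | no rule |
| Alcohol | not allowed | no rule | no rule | alcoholism only, as a cause of neuropathy |
| Coffee, tea | not allowed | no rule | no rule | no rule |
| Work or life pressure | not allowed | no rule | no rule | no rule |

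**Step 2: see which contrasts are exposed.**
- Healthy versus either diabetic group: exposed. Random allocation speaks of assigning participants at random to the three groups, but nobody can be randomised to being healthy or diabetic, so chance does not balance these factors.
- PDPN versus DM without PDPN: not exposed to this filter, because neither group has it.
- Electroacupuncture versus sham within a diabetic group: not exposed, because both arms share the same criteria and are randomised.

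**Step 3: illustrate the size.** The plan gives no figure to reproduce. Let p be the share of diabetic participants with the habit or stress (taken as 0 in the healthy group) and d its effect on an imaging measure in SD units. Both are assumptions; the documents give neither.

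Bias = p × d.

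Standard error for 30 versus 60 = √(1/30 + 1/60) = 0.224 SD.

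Two-sided rejection rate at 5% with no disease effect (normal approximation) = Φ(bias/SE − 1.96) + Φ(−bias/SE − 1.96).

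| p | d | Bias (SD) | 30 vs 60 | 30 vs 30 |
|---|---|---|---|---|
| 0.2 | 0.2 | 0.04 | 5.4% | 5.3% |
| 0.2 | 0.5 | 0.10 | 7.3% | 6.7% |
| 0.5 | 0.5 | 0.25 | 20.1% | 16.2% |
| 0.8 | 0.5 | 0.40 | 43.2% | 34.1% |
| 0.8 | 0.8 | 0.64 | 81.7% | 69.8% |

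For the middle row, 0.25/0.224 = 1.118, and Φ(−0.842) + Φ(−3.078) = 0.201.

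**Step 4: what adjustment can recover.** The healthy group has no users, so the effect of a habit can be estimated only among diabetic participants. With one yes/no habit and an additive model, there are three means: healthy, diabetic non-users and diabetic users. The adjusted disease effect is then exactly diabetic non-users minus healthy. With several habits, adjustment leans further on the model. A restricted comparison is therefore the more transparent check.

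Its precision depends on p. From 60 diabetic participants:
- p = 0.2 leaves 48: SE = √(1/30 + 1/48) = 0.233 SD.
- p = 0.5 leaves 30: SE = √(1/30 + 1/30) = 0.258 SD.
- p = 0.8 leaves 12: SE = √(1/30 + 1/12) = 0.342 SD.

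**The case against.** The strongest reply is about scope. The article does not spell out a healthy-versus-diabetic imaging contrast. The one group comparison described under Cerebral imaging index is PDPN against non-PDPN. The primary goal concerns PDPN participants before and after treatment, and the sample size rests on experimental versus control change in a pain questionnaire. The DM-without-PDPN group supplies a pain-free diabetic comparator without this filter, so a conclusion on central sensitization need not depend on the healthy group. All of this stands. What remains is that the article analyses all groups and includes an untreated healthy group, and every comparison that uses it is exposed.

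Other replies also stand:
- The size is assumed throughout. Pooling four substances and stress into one exposure with one direction is a simplification, and opposing effects would shrink the bias. The criterion may also mean habitual use rather than any use.
- Covariates for the imaging models may be set in a statistical plan that is not shown. The ANOVA without covariates appears under Clinical data analysis, not in the imaging section. A reader might infer that the trial will not adjust for habits; the article cannot establish that.
- A reader might see a contradiction with the Discussion's statement on baseline consistency. That statement is a general intention and names no matching variable.
- A reader might infer that the rule on pressure, which refers to the observation period, allows a healthy volunteer to be removed after scanning under Participant elimination criteria. The wording leaves room for this, but the article describes no such procedure.
- A tightly selected reference group is a defensible way to reduce noise. Trial status expects recruitment to end by December 2021, one month after publication. Dropping the criteria then would leave a reference group recruited under two rules.

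**Conclusion.** The asymmetry is explicit in the eligibility lists, and randomisation cannot remove it. Healthy-versus-diabetic imaging differences therefore cannot be separated from differences in habits and stress. This rests on the text and on the plausible premise that these factors can affect the imaging measures.

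The size is unknown. Under the assumed values it runs from negligible (5.4% rejections at a nominal 5%) to dominant (81.7%), and no point in that range can be preferred from the documents.

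Two stronger readings are not supported. One is that such differences show habits and stress rather than disease: the documents allow only that the two are mixed. The other is that the trial's treatment comparisons or its PDPN versus DM-without-PDPN comparison are biased by this rule: they are not. The point is a limit on what the healthy reference group can show, with an inexpensive remedy.

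**What to change.** 1. Record tobacco, alcohol, coffee and tea use and perceived stress in all 150 participants. The depression and anxiety measures under Secondary outcomes are listed for PDPN participants only, so they do not supply this record.
2. Give every group the same pre-scan instruction on these substances.
3. In any imaging comparison with the healthy group, adjust for these factors. Show the result with and without stress, since stress may partly follow from the disease.
4. Add a sensitivity analysis restricted to diabetic participants who report none of these habits.
5. State that differences from the healthy group will not be attributed to disease or central sensitization unless they persist in that analysis. Judge this on the estimate and its interval, because loss of significance in a smaller subset is not evidence that the difference has gone.

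The cost is a few case report form items and a less precise restricted analysis. If half of the 60 diabetic participants qualify, its standard error is 0.258 instead of 0.224 SD, about 15% larger; with 12 left it is 0.342 SD. For participants already scanned, habits would have to be collected retrospectively, with some recall error. The entry criteria themselves need not change.
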